## Abstract

**Background:**

Kidney transplant recipients receive maintenance immunosuppressive therapy to avoid allograft rejection resulting in increased risk of infections and infection-related morbidity and mortality. Approximately 98% of adults are infected with varicella zoster virus, which upon reactivation causes herpes zoster. The incidence of herpes zoster is higher in kidney transplant recipients than in immunocompetent individuals, and kidney transplant recipients are at increased risk of severe herpes zoster-associated disease. Vaccination with adjuvanted recombinant glycoprotein E subunit herpes zoster vaccine (RZV) prevents herpes zoster in older adults with excellent efficacy (90%), and vaccination of kidney transplant candidates is recommended in Danish and international guidelines. However, the robustness and duration of immune responses after RZV vaccination, as well as the optimal timing of vaccination in relation to transplantation remain unanswered questions. Thus, the aim of this study is to characterize the immune response to RZV vaccination in kidney transplant candidates and recipients at different timepoints before and after transplantation.

**Methods:**

The Herpes Virus Infections in Kidney Transplant Patients (HINT) study is a prospective observational cohort study. The study will include kidney transplant candidates on the waiting list for transplantation (*n* = 375) and kidney transplant recipients transplanted since January 1, 2019 (*n* = 500) from all Danish kidney transplant centers who are offered a RZV vaccine as routine care. Participants are followed with repeated blood sampling until 12 months after inclusion. In the case of transplantation or herpes zoster disease, additional blood samples will be collected until 12 months after transplantation. The immune response will be characterized by immunophenotyping and functional characterization of varicella zoster virus-specific T cells, by detection of anti-glycoprotein E antibodies, and by measuring cytokine profiles.

**Discussion:**

The study will provide new knowledge on the immune response to RZV vaccination in kidney transplant candidates and recipients and the robustness and duration of the response, potentially enhancing preventive strategies against herpes zoster in a population at increased risk.

**Trial registration:**

ClinicalTrials.gov (NCT05604911).

**Supplementary Information:**

The online version contains supplementary material available at 10.1186/s12879-023-08663-5.

## Background

For a selected group of patients with chronic kidney failure, kidney transplantation is the best treatment modality. After transplantation, kidney transplant recipients receive life-long immunosuppressive maintenance therapy to avoid rejection of the transplanted organ, resulting in an increased risk of infections and infection-related morbidity and mortality [1].

Varicella zoster virus (VZV) causes varicella during primary infection and herpes zoster when reactivated. In Denmark, primary vaccination against VZV is not recommended by health authorities [2], and varicella is a common childhood infection. Thus, 98% of solid organ transplant candidates in Denmark are sero-positive towards VZV [3] indicating a prior primary VZV infection. To avoid herpes zoster, cellular immunity towards VZV is important [4, 5]. However, the main target of immunosuppressive maintenance therapy post-transplantation is T cells, thus hampering the cellular immunity. The crude incidence of herpes zoster in kidney transplant recipients has been reported to be 6.7% [6], and kidney transplant recipients are at higher risk of herpes zoster than immunocompetent individuals [7–9]. Furthermore, kidney transplant recipients are at increased risk of severe herpes zoster disease and post-herpetic neuralgia [9–11].

Shingrix® (GlaxoSmithKline) is an adjuvanted recombinant glycoprotein E subunit herpes zoster vaccine (RZV). RZV prevents herpes zoster in older adults with 90% efficacy [12, 13]. A randomized clinical trial reported 68% RZV efficacy in hematopoietic stem cell transplant recipients [14], but the efficacy of RZV in kidney transplant recipients has not been established. RZV has been reported to be immunogenic and safe in kidney transplant recipients [15, 16], and RZV vaccination of kidney transplant candidates and recipients is recommended in both international and Danish guidelines [17, 18]. Although it has been suggested that cellular immunity towards VZV after natural infection and live attenuated vaccination persist over the course of transplantation [19, 20], the robustness and duration of immune responses after RZV vaccination in kidney transplant candidates and recipients, as well as the optimal timing of vaccination has not been established. Thus, characterization of immune responses to herpes zoster infection at different time points in relation to kidney transplantation might enable better preventive strategies in a population at high risk.

### Study objectives

In kidney transplant candidates and recipients receiving RZV at different time points before and after transplantation we aim to determine:

#### Primary aim

The T cell immunity towards VZV determined by deciphering the size, specificity and fitness of the T cell response following RZV, and the protective role towards herpes zoster.

#### Secondary aims

The anti-glycoprotein E antibody response rate and risk factors for anti- glycoprotein E antibody non-response.

The persistence of anti-glycoprotein E antibody and T cell immune responses.

## Methods

The Herpes Virus Infections in Kidney Transplant Patients (HINT) study is a prospective observational cohort study. Kidney transplant recipients transplanted after January 1, 2019, and kidney transplant candidates on the waiting list for kidney transplantation at Copenhagen University Hospital – Rigshospitalet, Odense University Hospital, or Aarhus University Hospital who are offered a RZV vaccine will be invited to participate in the study until February 1, 2025. Recruitment of participants started January 16, 2023 and is currently ongoing.

The kidney transplant centers at Copenhagen University Hospital – Rigshospitalet, Odense University Hospital, or Aarhus University Hospital are responsible for the inclusion and follow-up of participants, while researchers from the department of health technology at Technical University of Denmark (DTU) are responsible for the immunological analyses. The study is performed in collaboration with the herpesvirus immunology in solid organ transplant recipients – liver transplant study (HISTORY) and parts of the methodology follows what has previously been described in the HISTORY study protocol [21]. A STROBE [22] checklist is provided as supplementary material (supplementary material).

### Vaccinations

All participants who accept the offer to receive RZV vaccination are vaccinated according to Danish guidelines at their local transplant center. Therefore, vaccinations are performed uniformly at all three centers by administering two doses of vaccine with two months between each dose. All vaccinations administered are a part of routine clinical care.

### Eligibility criteria

Participants must be either on the waiting list for kidney transplantation OR first time transplanted after January 1, 2019, AND above 18 years old, able to provide informed consent, and have been offered a RZV vaccine. Patients are eligible to participate whether they accept RZV vaccination or not.

### Blood sampling

Venous blood samples are collected from participants at scheduled visits to the clinical sites. All participants will provide a blood sample at inclusion i.e., at the time they are offered the first dose of RZV vaccination. Hereafter, all participants will be invited for repeated blood sampling 1, 2, 6, and 12 months after the first dose of RZV was offered. Furthermore, participants who are on the waiting list for transplantation and transplanted during the study will be invited for blood sampling at 6 and 12 months after transplantation. If a participant develops herpes zoster during the study period, they will be invited for blood sampling immediately after the infection has been diagnosed. At each sample time, 60 mL of venous blood will be collected in lithium-heparin and EDTA-coated collection tubes.

Within 4 h after collection, blood collected in lithium-heparin-coated collection blood tubes will be transported to the laboratory for purification of peripheral blood mononuclear cells (PBMC) using density gradient centrifugation. EDTA-coated collection tubes will be stored on ice immediately after collection and centrifuged within 1 h, after which plasma will be separated and stored at -80 °C. After primary processing at either Copenhagen University Hospital – Rigshospitalet, Odense University Hospital, or Aarhus University Hospital, all PBMC and plasma samples will be stored in liquid nitrogen at a biobank at the Department of Health Technology, DTU.

### Questionnaire

At inclusion, participants will be asked to fill out a questionnaire about health, lifestyle, socioeconomic status, current and previous use of medication and vaccinations. The questionnaire will be entered directly into REDCap [23]—a secured digital platform or on paper (supplementary material). At each following study visit, participants will be asked to fill out a questionnaire regarding changes related to transplantation, vaccinations, rejection episodes, and infections since the last study visit (supplementary material).

### Antibody assay

The anti-glycoprotein E antibody response rate will be determined by Enzyme-Linked Immunosorbent Assay (ELISA). Glycoprotein E is the main target for VZV-specific immune responses [24]. We will establish and validate a previously reported ELISA and measure anti-glycoprotein E antibody concentrations in plasma samples collected from all participants at all time points. The anti-glycoprotein E antibody response rate will be defined as the percentage of subjects with anti-glycoprotein E antibody concentration ≥ 4-fold higher than at baseline.

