#### Statistical analyses

Continuous data will be compared using Student’s t test or Mann–Whitney U test, and categorical data will be compared using Pearson’s χ^2^ or Fisher’s exact tests, as appropriate. Mixed linear models will be used to evaluate the development of antibody and T cell immunity towards VZV over time and to explore risk factors for non-response.

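### The antibody response rate is a 4-fold rise over own baseline with no stated baseline adjustment, so differences in baseline antibody may pass for differences in vaccine response

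*Protocol article*

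**What the plan says.** - **Response definition** (Antibody assay): the response rate is the share of participants whose anti-glycoprotein E concentration is at least "4-fold higher than at baseline". No absolute level and no rule by baseline level accompanies it. The same section has the concentration measured in every participant at every time point.
- **Population** (Background): "98% of solid organ transplant candidates in Denmark are sero-positive towards VZV".
- **Aim served** (Secondary aims): the antibody "response rate and risk factors for anti- glycoprotein E antibody non-response".
- **Baseline sample** (Blood sampling): "All participants will provide a blood sample at inclusion i.e., at the time they are offered the first dose of RZV vaccination".
- **Analysis** (Statistical analyses): "categorical data will be compared using Pearson’s χ^2^ or Fisher’s exact tests, as appropriate". The section then adds: "Mixed linear models will be used to evaluate the development of antibody and T cell immunity towards VZV over time". The same sentence gives these models the exploration of risk factors for non-response. It lists no covariates.
- **Use of the result** (Discussion): the investigators expect the comparison of vaccination times to establish the best timing, and expect the risk factors to guide surveillance and possible booster doses.

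**The concern.** The baseline concentration is the denominator of the outcome. Unless log post-vaccination concentration rises one-for-one with log baseline, the chance of meeting the 4-fold criterion changes with the starting level. When the slope is below 1, a higher starting level lowers that chance. Most participants can be expected to start with some VZV antibody, so baseline is unlikely to be uniformly near zero.

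Two results are exposed. First, any characteristic that goes with a higher baseline could appear as a risk factor for non-response, although it may only mark existing antibody. Second, the waiting-list group and the three recipient groups may differ in baseline. A crude comparison of their response rates would then mix that difference with any real difference in response, and the Discussion intends to draw a conclusion on timing from this kind of comparison.

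**Working it through.** The plan has no calculation of its own to reproduce: Sample size says that a formal one cannot be done. The check below shows when the mechanism operates and how large it could be.

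**Inputs from the protocol article.** The threshold is 4-fold. The planned groups are 375 on the waiting list and 250, 125 and 125 recipients (6–12, 12–24 and more than 24 months after transplantation).

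**Assumptions, not in the documents.** Baseline SD 0.5 log10, residual SD 0.45 log10, a 10-fold rise at the reference group's mean baseline, and one group with a 2-fold higher mean baseline (d = log10 2 = 0.301). The slope b of log post-vaccination level on log baseline runs from 0 to 1. Both groups have the same post-vaccination level for a given baseline.

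**Formula.** The log10 fold rise in a group whose mean baseline is shifted by d is normal, with mean 1 − (1 − b)d and SD S = √(0.45² + ((1 − b) × 0.5)²). With log10 4 = 0.602,

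P(response) = Φ((0.398 − (1 − b)d) / S).

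**Example, b = 0.3.** S = √(0.2025 + 0.1225) = 0.570.
- Reference group: Φ(0.398 / 0.570) = Φ(0.698) = 75.7%.
- Group with higher baseline: Φ((0.398 − 0.7 × 0.301) / 0.570) = Φ(0.328) = 62.9%.
- Gap: 12.9 points before rounding.

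| Slope b | Lowest baseline quartile | Highest baseline quartile | Reference group | 2-fold higher baseline | Gap (points) |
|---|---|---|---|---|---|
| 0 | 98% | 33% | 72% | 56% | 17 |
| 0.3 | 96% | 47% | 76% | 63% | 13 |
| 0.6 | 92% | 62% | 79% | 71% | 8 |
| 0.8 | 88% | 73% | 81% | 77% | 4 |
| 1 | 81% | 81% | 81% | 81% | 0 |

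The quartile columns are for the reference group.

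**Against sampling error.** At b = 0.3 the 95% half-width for the difference is:
- 125 vs 125: 1.96 × √((0.757 × 0.243 + 0.629 × 0.371) / 125) = 11 points.
- 375 vs 250: 1.96 × √(0.757 × 0.243 / 375 + 0.629 × 0.371 / 250) = 7 points.

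At slopes of about 0.3 or less, the gap exceeds the half-width for either pair of groups. At 0.6 it is 8 points against 11 (125 vs 125) and 7 (375 vs 250). At 0.8 it lies inside both.

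**Sensitivity.** With both SDs at 0.45 and a 2-fold baseline difference, a mean rise of 8-fold gives 73% vs 62% at b = 0.5 and 68% vs 50% at b = 0. A mean rise of 15-fold gives 87% vs 80% and 82% vs 67%. At b = 1 there is again no gap.

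**The case against.** The case on the other side is substantial.

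- **Antibody is not judged only by the 4-fold rule.** A reader might infer this from the definition, but Statistical analyses also plans mixed linear models of antibody over time and gives them the risk factors for non-response. The concern therefore applies to the response rate and its crude comparison. It reaches the models only in that no baseline adjustment is named. An unlisted covariate is, taken alone, something that an article may leave to a fuller document. What the article does fix is the ratio definition and the unadjusted tests.
- **High-baseline patients are not simply non-responders.** That reading is tempting but wrong: in the table, 33% to 81% of the highest quartile still respond.
- **The timing groups are not shown to be non-comparable.** The documents give no baseline anti-glycoprotein E level, overall or by group. The 98% is VZV serostatus in transplant candidates, which says nothing about concentration or spread. Baseline is also measured in everyone, so adjustment remains possible.
- **The bias is conditional.** At slope 1 it vanishes, and the documents neither show nor exclude that slope. Random assay error in the baseline reading pulls the observed slope down, so exactly 1 is a special case, but a slope near 1 would leave little bias.
- **A relative criterion is reasonable here.** With near-universal seropositivity, a seropositivity threshold would count almost everyone as a responder before vaccination.
- **Adjustment is not neutral.** The groups are not randomised, and recipients' baseline is sampled after transplantation, so it may itself reflect immunosuppression. Conditioning on it may remove part of the timing effect of interest. The calculation takes equal response at a given baseline as the truth, which is one choice of question.

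The last point stands in full and shapes the remedy: adjusted results should accompany the crude ones, not replace them.

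**Conclusion.** The point holds in a conditional form. The response rate depends on own baseline by construction, and neither the tests for categorical data nor the models are stated to account for it. If the slope of log post-vaccination level on log baseline is below 1, a higher baseline raises the chance of being classed as a non-responder. If the timing groups also differ in baseline, part of any gap between their response rates may reflect that difference. Under the assumed values the part due to baseline runs from 17 points at slope 0 to none at slope 1. Both the slope and the 2-fold group difference are assumptions. Severity is moderate: the aim is secondary and the study is declared descriptive and exploratory, but the Discussion looks to the timing comparison for guidance.

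**What to change.** Amend Statistical analyses, or the analysis plan if one exists, as follows:

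1. Keep the 4-fold response rate as a descriptive figure for each timing group.
2. Beside it, compare post-vaccination log anti-glycoprotein E concentration between timing groups with log baseline concentration as a covariate, reported as adjusted geometric mean ratios with confidence intervals.
3. Include log baseline as a covariate in whatever model is used for non-response.
4. Report the unadjusted comparison as well, and state that the two answer different questions: one compares groups as they stand at vaccination, the other compares participants with the same starting level.

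The cost is a little more analysis and two estimates to interpret. Baseline samples are already collected and assayed in all participants, so no new data are needed.

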### Identification of VZV specific T cells

To identify the complete repertoire of VZV-specific T cells and their immunodominance towards VZV, we will perform a broad T cell screening towards potential T cell epitopes in VZV, as previously described [21]. Human leukocyte antigen (HLA)-class I presented epitopes will be predicted (NetMHCpan-4.1) and synthetized to make peptide-HLA multimers matching the HLA profile of the individual participant (Fig. 1). We will cover the 12 most frequent HLA haplotypes [25]. Using DNA-barcode labeled peptide-major histocompatibility complex (pMHC) multimers and subsequent flow cytometry-based sorting of VZV-specific T cells, we can determine the T cell recognition to a large library of potential epitopes (> 1000/sample) [26, 27]. The sequential sampling pre- and post-transplantation will allow a comparative assessment and monitoring of T cell frequency, phenotype and fitness at different levels of immunosuppression.

**Fig. 1 Fig1:**
[figure not shown]
Overview of methods for identification and evaluation of T cells using peripheral blood mononuclear cells

Using the NetMHCpan 4.1 platform, as previously described in the HISTORY study protocol [21], potential varicella-zoster virus (VZV) peptide-MHC (pMHC) complexes will be predicted corresponding to the most frequent HLA haplotypes amongst participants. The pMHC complexes will be combined in a DNA-barcoded patient-specific pMHC multimer. Peripheral blood mononuclear cells (PBMCs) will be examined for their detection of pMHC multimers and sorted using flow cytometry based on their expression of phenotypic cell surface markers. The reactive T cells may be further examined for their frequency, T cell receptor sequence, and potential for ex vivo expansion [21].

### Phenotype and cytokine profiling

Phenotyping and functional characterization of specific T cell populations towards immunodominant epitopes in VZV will be carried out, as previously described in the HISTORY study protocol [21], by using a flow cytometry panel of 13 cell surface and intracellular markers of activation, senescence, and exhaustion (Fig. 1). Furthermore, we will measure the cytokine profiles in plasma samples using an established Luminex MILLIPLEX assay to simultaneously quantify 41 analytes that map the complete cytokine signature including interleukins, chemokines, and growth factors (Fig. 2).

**Fig. 2 Fig2:**
[figure not shown]
Overview of methods for cytokine profiling using Luminex MILLIPLEX® assay

Cytokine profiling will be performed as previously described in the HISTORY study protocol [21]. Plasma contains an unspecified concentration of analytes of interest, i.e. cytokines, chemokines, interleukins and growth factors. To determine the concentration of the analytes, each Luminex well contains multiple types of color-coded beads conjugated to a capture antibody that binds the specific analyte of interest. In presence of the analyte, a biotin-conjugated detection antibody will bind to the capture antibody-analyte complex. Adding phycoerythrin-labeled streptavidin will produce fluorescence that is color-specific for each analyte and allows for measurement of the mean fluorescence intensity (MFI) of each analyte in each Luminex well. Comparing MFI at different dilution levels with standard solutions allows for determination of the concentration of the analytes of interest.

### T cell receptor sequencing

We will apply a technology that allows for large-scale collection of T cell receptor (TCR) sequences paired to different peptide targets based on their pMHC recognition motif through a pMHC multimer linked to a DNA barcode [28]. Using single-cell capture and analysis systems based on sorted pMHC responsive T cells, we can pair the TCR sequences and assign the pMHC specificity based on the co-attached DNA barcode. Using this platform, we will identify T cell clonotypes of relevance for VZV recognition and describe their functional characteristics. We will implement parallel phenotyping of immune cells using a 150 + marker panel of DNA barcoded antibodies that target a broad array of lineage markers, activation markers, exhaustion markers, and regulatory markers.

### Clinical data

Data on demographics, comorbidities, biochemistry, medication, allograft rejection, pathology, HLA, and hospital admissions will be collected from electronical hospital records. All Danish hospital records since 1 December 2010 are accessible through a nationwide digital platform. Data on vaccinations will be collected through the Danish vaccination register (DDV) [29]. Since 2015, it has been mandatory to register all vaccinations administered in Denmark in DDV. Data on infections will be collected from the Danish Microbiology database (MiBa) [30], which is a nationwide database including all microbiological samples collected at both hospitals and general practitioners in Denmark.

### Statistics

#### Sample size

The purpose of the study is to describe the T-cell and anti-glycoprotein E antibody response to RZV and herpes zoster in kidney transplant candidates and recipients and to explore factors for immune non-response at different times before and after transplantation. In Denmark about 390 patients are active on the waiting list for kidney transplantation and about 250 kidney transplantations are performed each year [31]. We aim to include 250 kidney transplant recipients who are 6–12 months from transplantation, 125 who are 12–24 months from transplantation, and 125 who are > 24 months. Furthermore, since some of the transplant candidates may not be transplanted during the study period, we will include 375 patients who are on the waiting list. Given the descriptive and exploratory scope of the study and lack of existing data regarding outcomes of interest, a formal sample size calculation cannot be conducted. The study is not powered for clinical efficacy estimates.

